**Background**

Dental caries is one of the most common chronic infectious diseases in the world [[Anusavice, 2002](#_ENREF_2)]. Despite the massive impact of dental caries on global welfare, the mechanisms of action and effective prevention and treatment in the susceptible fraction are insufficiently defined [[Lancet, 2009](#_ENREF_11)].

Research regarding probiotics to prevent oral diseases has increased in recent years. There is a concept where these “beneficial” microorganisms can inhibit a detrimental biofilm formation and protect oral tissue from disease [[Caglar et al., 2005](#_ENREF_4); [Meurman and Stamatova, 2007](#_ENREF_14)]. The most common probiotic strains belong to the genera *lactobacillus* and *bifidobacterium* [[Meurman and Stamatova, 2007](#_ENREF_14)]. Lactobacilli species have been associated with the development of dental caries because their aciduric and acidogenic traits [[Van Houte, 1980](#_ENREF_25)], however, they have also been linked to beneficial probiotic traits by mechanisms that include ecology modulation and immune stimulation [[McFarland, 2000](#_ENREF_13); [Mikelssar et al., 2004](#_ENREF_15); [Perdigón et al., 2001](#_ENREF_17)].

*L. reuteri* is a Gram-positive, non-sporeforming, non-motile, facultative anaerobic rod shaped bacillus [[Sinkiewicz, 2010](#_ENREF_22)] which produces a number of antibacterial compounds including, reuterin, a broad-spectrum antimicrobial structurally related to hydroxylpropionaldehyde [[Reuter, 2001](#_ENREF_18)]. Colonization of probiotic bacteria is considered an important event in establishing their beneficial effects. The mechanism of colonization/adherence in the gastrointestinal (GI) tract, i.e. “how” this occurs is unknown. However, colonization of the GI can be improved when *L. reuteri* is exposed to mucin [[Roos and Jonsson, 2002](#_ENREF_19)]. Long-term colonization by probiotic bacteria seems unlikely and bacteria has been only detected during the time probiotic products are in active use [[Haukioja, 2010](#_ENREF_6)].

We recently reported that *L. reuteri* strains DMS 17938 could colonize the oral cavity of 60-70% of subjects consuming them [Vestman *et al*., 2013]. In that study we also developed two selective media and presented specific primers for identification of *L. reuteri* DMS 17938 and ATCC PTA 5289.

**Aim**

In the present study, we attempt to *(i)* determine the profile of small molecules in supragingival plaque (teeth)*, and* *(ii)* to compare the oral microbiota between individuals with and without exposure of *L. reuteri* in a longitudinal RCT design and by use of pyrosequencing analysis.

**Hypothesis**

*L. reuteri* would influence biofilm ecology towards a less cariogenic microbiota and consequently showed variation in the metabolic profile.

**Methods**

**Study group**

Healthy volunteers will be recruited by advertising on boards at the Faculty of medicine, University of Umeå, Sweden. The inclusion criteria will be: *(i)* healthy with no reported medical condition and no active caries lesions or periodontitis. *(ii)* no use of antibiotics the last 3 months , *(iii)* no reported probiotic consumption 3 months prior to the study and *(iv)* no smoking. Based on previous knowledge of acquisition of probiotic bacteria, at least 40 individuals will be included in this study. Ethical approval will be obtained and all participants will be asked for a written consent at their baseline visit.

**Study design and intervention**

The study design is an explorative, double blinded, placebo-controlled randomized clinical trial with an exposure period of 12 weeks and 1- and 6- month follow-ups. Subjects will be randomly selected to a test or a control group using SPSS. Randomization will be done by a person that will not participate in sample collection. During the intervention period subjects will be asked to let one lozenge slowly melt in the mouth twice a day. The test lozenges contain *L. reuteri* (DSM 17938 and PTA 5289; 10^8^ CFU per strain; BioGaia AB, Stockholm, Sweden), isomalt, hydrogenated palm oil, peppermint and menthol flavoring, peppermint oil, and sucralose (<http://www.biogaia.com/product/biogaia-prodentis-oral-lozenges>). The safety of the lozenges has been documented and they are commercially available as an over the counter product. Except for the lactobacilli, the placebo lozenge are identical in composition, appearance and taste to the test lozenge.

**Microbiological Sampling**

Samples (saliva and dental biofilm) will be obtained at baseline and at 4, 8 and 12 weeks during *L. reuteri* exposure. Follow-up samples will be collected 1 and 6 months after finishing the exposure period. Stimulated saliva (~5mL) will be collected into ice chilled sterile test tubes during chewing on paraffin, and ~1mL of saliva will be used for cultivation on selective and not selective agar plates in our laboratory. The remaining saliva will be centrifuged and stored at -80ºC (pellets and supernatant separately) for pyrosequencing analysis. Lozenges extracts will also be cultivated to control presence/absence of lactobacilli, and grown lactobacilli would be identified by species/strain specific culturing combined with 16S rDNA PCR amplification and sequencing. Biofilm will be sampled with sterile tooth-picks from available smooth tooth surfaces in the premolar/molar and upper incisor regions. Pooled biofilm will be divided into two portions, one for metabolomics and one in TE-buffer for DNA extraction for the pyrosequencing. Samples will be stored in sterile Eppendorf tubes at -80°C until analysed.

**GC-TOFMS metabolomics for fingerprinting of small molecules**

The protocol for GC-TOFMS follows [Wuolikainen et al. [2011](#_ENREF_27)]. Thus, low molecular weight compounds/metabolites are extracted from tooth biofilm samples with methanol/water supplied with labeled internal standards. The extracts are derivatized by addition of *O*-methylhydroxylamine hydrochloride in pyridine and an injection standard (methylstearate) is added. For the GC-TOFMS analysis 1 μL aliquot is injected splitless into a gas chromatograph equipped with a 10 m fused-silica capillary column chemically bonded with 0.18 μm DB 5-MS stationary phase. The injector temperature is set to 270°C and the septum purge gas is turned on after 60 s at a flow rate of 20 mL/min. The initial column temperature is 70 °C for 2 min, followed by increases by 40°C /min until a temperature of 320°C is reached. The oven is then allowed to return to and stabilize at the starting temperature. The gas flow rate through the column is 1 mL/min. The column outlet is connected to the ion source of a Pegasus III TOFMS. Transfer line temperature is set to 250°C and ion source temperature to 200°C. Ions are produced by a 70 eV electron beam (2.0 mA). Acceleration voltage is switched on after a 165 s solvent delay and masses are acquired between *m/z* 50-800, at a rate of 30 spectra s-1 for 445 s.

Settings for resolving chromatographic profiles are rated by maximum number of resolved profiles, minimum number of bad spectra, splitting of internal standard peaks and library hit of internal standards. Detected metabolites are identified by chromatographic retention times, and resolved mass spectra are compared against in-house and publicly available mass spectra libraries (NIST 98 mass spectra library, the Umeå Plant Science Centre mass spectra library and the mass spectra library hosted by the Max Planck Institute) or *de novo* identification. Unknown metabolites will (if possible) be categorized into chemical classes, such as fatty acid, amino acid, etc. Data will be normalized to the 11 internal standards and the injection standard.

**Pyrosequencing for detection of the complex microbiota**

Biofilm samples will be analyzed with 454 pyrosequencing either the bench top GS Junior machine or FLX+ with titanium chemistry (Roche). This should yield between 100 000 to 1 000 000 reads with a sequence mean length of at least 400 basepairs (bp). Ligation of a sample-specific barcodes allow several samples to be run simultaneously. There are four major steps in pyrosequencing. (1) library construction, including DNA extraction, purification and concentration, 16S rDNA amplification using universal primers amplifying a 600-bp segment in the V3-V4 hypervariable region of the 16S rRNA gene, ligation of 21 bp 3’ and a 5’ titanium adaptor sequences, and the barcode for sample origin recognition. The library may be stored at-20°C for months. (2) Emulsion amplification where capture beads carrying one ligated PCR reagent/bead is placed into a water in oil microreactor (droplet), in which amplification takes place (using universal primers to the adaptor sequences). (3) Sequencing of fragments on DNA positive beads placed in nano-wells on a slide after breaking the microreactors and enrichment of amplicon carrying beads. (4) Data processing include trimming, quality filtering and chimera removal using the QIIME pipeline. Sequences will be clustered into OTUs at 97% similarity against the Greengene database and taxonomically identified against the HOMD database. Identified species/phylotypes will be further analyzed by traditional univariate analyses for means and proportions and multivariate projection methods.

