**Statistical power**

Previous studies using probiotic products have shown statistically significant effects on mutans streptococci in groups of 20 subjects with high levels of mutans streptococci. We will recruit at least 40 subjects to ensure that we have a sufficient number of subjecta were the test bacteria is retained during exposure and to get subjects with different levels of mutans streptococci to facilitate effects in strata of mutans streptococci levels, and to account for that some subjects for some reason will terminate their participation.

Data will be analyzed using SIMCA 12+ and SAS depending on character of the analysis. For description means (95%CI) and proportion distributions will be calculated and differences between groups will be tested with parametric or non-parametric tests depending on data character and distribution. For most parts of the analyses multiple comparison adjustments by the false discovery rate (recommended for large number of measures such as in genome wide arrays) will be applied. Multivariate analyses will be done with PCA, PLS(-DA), and OPLS-(DA). Prior to multivariate data analysis GC-TOFMS internal standards and methylstearate are excluded and all data are mean centred and scaled to unit variance. This method has been very useful for datasets where the number of variables exceeds the number of cases and where variables co-vary [[Kanasi et al., 2010](#_ENREF_10)].

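### No step sets aside the L. reuteri dosed in one arm only, so at the exposure visits its own reads can separate the arms without any change in a resident taxon

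*Protocol*

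**What the plan says.** The pyrosequencing section describes universal-primer sequencing of tooth biofilm ("16S rDNA amplification using universal primers amplifying a 600-bp segment in the V3-V4 hypervariable region of the 16S rRNA gene"), clustering into OTUs and taxonomic identification. It then says: "Identified species/phylotypes will be further analyzed by traditional univariate analyses for means and proportions and multivariate projection methods". No taxon is excepted.

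The Statistical power section names PCA, PLS(-DA) and OPLS-(DA), applies the false discovery rate to most analyses, and gives the only stated preparation step: "Prior to multivariate data analysis GC-TOFMS internal standards and methylstearate are excluded and all data are mean centred and scaled to unit variance". The items removed there are laboratory additions to the metabolite samples. The section says nothing about the organism that the intervention adds.

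The lozenges differ in one respect only: "Except for the lactobacilli, the placebo lozenge are identical in composition, appearance and taste to the test lozenge". Samples "will be obtained at baseline and at 4, 8 and 12 weeks during" exposure, and again 1 and 6 months after it ends. The Background reports that in an earlier study the test bacteria "could colonize the oral cavity of 60-70% of subjects consuming them". It also says of probiotics in general that "bacteria has been only detected during the time probiotic products are in active use".

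**The concern.** While lozenges are being taken twice daily, L. reuteri sequence in plaque shows in the first place that the test arm was dosed. Nothing in the plan separates that from a response of the resident flora. If the dosed species is one of the variables compared, three things follow.

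- A univariate test can flag it.
- A discriminant model can use it to separate the arms. Unit-variance scaling gives it the same starting weight as a dominant resident species.
- Because relative abundances sum to one, its reads lower the share of every other taxon in the test arm.

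The Significance section presents the study as settling whether probiotic exposure modifies the biofilm. A separation of the arms that rests on the dosed organism could be reported under that broad statement although no resident taxon had moved.

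**Working it through.** **Inputs from the protocol.** At least 40 subjects; oral-cavity carriage of 60-70% among consumers; six samplings, three of them during exposure; a stated yield of 100 000 to 1 000 000 reads, with no statement whether this is per run or per sample.

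**Assumptions.** 1:1 allocation with 20 analysed per arm; FDR level 0.05; 100-300 taxa tested (200 for the threshold below); placebo carriage 0 unless stated; oral-cavity carriage applied to plaque. The protocol fixes none of these.

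**The plan's own figure.** The 40 subjects equal 2 x 20, the group size the protocol cites from earlier studies. With no effect size or power given, it cannot be derived further, and nothing below depends on how it was reached.

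**1. Univariate detection.** Two-sided Fisher test. With k of 20 positive against 0 of 20, p = 2 x C(20,k)/C(40,k). For k = 12: 2 x 125 970 / 5 586 853 480 = 4.5e-5. The Benjamini-Hochberg threshold for the smallest p-value among 200 taxa is 0.05/200 = 2.5e-4.

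| Test v placebo carriers | p | Below 2.5e-4? |
|---|---|---|
| 14/20 v 0/20 | 3.3e-6 | yes |
| 13/20 v 0/20 | 1.3e-5 | yes |
| 12/20 v 0/20 | 4.5e-5 | yes |
| 12/20 v 1/20 | 4.3e-4 | no |
| 9/20 v 0/20 | 1.2e-3 | no |
| 6/20 v 0/20 | 0.020 | no |

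**2. Chance of at least one FDR-significant taxon when no resident taxon differs (simulation).**

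| Plaque carriage, test arm | 100 taxa | 300 taxa |
|---|---|---|
| 70% | 99% | 96% |
| 60% | 89% | 76% |
| 30% | 11% | 7% |
| L. reuteri removed | about 5% | about 5-6% |

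**3. Discriminant models.** In simulated unit-variance data with 50-300 null taxa, L. reuteri had the largest weight on the first PLS-DA component in 85-97% of runs at 60% carriage and 96-99% at 70%. At 30% this fell to 14-46%. In a separate null simulation with 50-200 other taxa, adding one such marker at 60-70% carriage raised the chance of a positive cross-validated PLS-DA fit from about 12-18% to 37-78%.

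**4. Dilution of resident proportions.** If L. reuteri takes a share x of reads, a resident proportion p becomes p(1 - x), a relative fall of x. The documents give no value for x. With 20 per arm and an assumed between-subject coefficient of variation of 50% or 100%, x = 10% raises the chance of a nominal p < 0.05 for one resident taxon from 5% to about 9% or 6%. With x = 1% it stays at 5%.

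**5. Read depth.** If the stated yield were one run shared by 40 x 6 = 240 samples, each sample would have about 417 to 4167 reads (100 000/240 to 1 000 000/240). The chance of seeing an organism at abundance a in r reads is 1 - (1 - a)^r. At a = 0.1% that is 34-98%; at a = 1% it is 98-100%. Low depth would therefore weaken the effect.

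**The case against.** **The protocol is silent rather than wrong.** It does not say that every taxon must be tested, and the sentence on exclusions names metabolomics reagents, not sequence features. Taxon filtering often belongs in an analysis plan. This is partly right: the sentence does not settle sequence filtering. But the protocol does state what goes into the comparison, and followed as written it leaves the one-arm organism in.

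**Colonisation is of interest in itself.** The Aim compares the microbiota with and without exposure, the Background treats colonisation as important, and the sample size anticipates subjects who retain the bacteria. This stands, and it is why both comparisons should be shown. A reader might infer that the hypothesis concerns only the rest of the biofilm, but the Hypothesis section does not say so.

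**A hit would be recognised.** Testing is at species or phylotype level, so a significant L. reuteri result would carry its name. This stands for univariate lists. It does not correct the fit of a discriminant model or re-normalise the other proportions, and nothing in the plan requires the check.

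**Stronger readings.** A reader might infer that the trial would falsely confirm its hypothesis. The documents do not support that: the design is called explorative, there is no rule that one significant taxon counts as confirmation, and the hypothesis is directional (less cariogenic), which the presence of L. reuteri alone does not show. A reader might also fear that a lactobacillus total or a cariogenic score would be distorted, but neither is planned. The metabolomic aim uses no reads.

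**Conclusion.** The point holds in limited form. As written, the dosed organism's own reads can contribute to or drive arm separation at weeks 4, 8 and 12, and this could be reported as a biofilm modification when no resident taxon changed.

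The effect is strong if plaque carriage is near the 60-70% quoted for the oral cavity and placebo carriage is nil. It weakens quickly otherwise: one placebo carrier against 12/20, or 45% carriage, already misses the assumed threshold, and at 30% little remains. Carriage in plaque, arm size, number of taxa and FDR level are all assumptions.

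It would go too far to say that resident proportions are materially biased, because the dilution equals an unknown read share and is minor if that share is low. It would also go too far to say that the whole trial is affected. By the Background's own account of detection during active use, the 1- and 6-month follow-ups should be largely untouched.

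**What to change.** In the pyrosequencing section, add three statements:

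1. For the between-arm comparison of the resident microbiota, reads assigned to L. reuteri are removed and proportions re-normalised before any univariate or multivariate test.
2. L. reuteri detection is reported separately, by arm and visit, as a measure of exposure or retention.
3. The same comparison with L. reuteri included is shown alongside.

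The cost is one filter step in the existing pipeline and a second run of the analysis, with no new samples or subjects. The small downside is that any native L. reuteri drops out of the resident comparison; the comparison shown alongside still contains it.

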**Statistical power**

Previous studies using probiotic products have shown statistically significant effects on mutans streptococci in groups of 20 subjects with high levels of mutans streptococci. We will recruit at least 40 subjects to ensure that we have a sufficient number of subjecta were the test bacteria is retained during exposure and to get subjects with different levels of mutans streptococci to facilitate effects in strata of mutans streptococci levels, and to account for that some subjects for some reason will terminate their participation.

Data will be analyzed using SIMCA 12+ and SAS depending on character of the analysis. For description means (95%CI) and proportion distributions will be calculated and differences between groups will be tested with parametric or non-parametric tests depending on data character and distribution. For most parts of the analyses multiple comparison adjustments by the false discovery rate (recommended for large number of measures such as in genome wide arrays) will be applied. Multivariate analyses will be done with PCA, PLS(-DA), and OPLS-(DA). Prior to multivariate data analysis GC-TOFMS internal standards and methylstearate are excluded and all data are mean centred and scaled to unit variance. This method has been very useful for datasets where the number of variables exceeds the number of cases and where variables co-vary [[Kanasi et al., 2010](#_ENREF_10)].

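### The protocol's own colonisation and group-size figures do not support the statement that 40 subjects ensure enough retainers while also serving strata and drop-out

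*Protocol*

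**What the plan says.** The protocol gives a minimum of 40 subjects in two places, with different reasons.

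- **Study group:** "Based on previous knowledge of acquisition of probiotic bacteria, at least 40 individuals will be included in this study". No calculation follows.
- **Statistical power:** the precedent is "statistically significant effects on mutans streptococci in groups of 20 subjects with high levels of mutans streptococci". The section then states: "We will recruit at least 40 subjects to ensure that we have a sufficient number of subjecta were the test bacteria is retained". The same sentence adds two further purposes for these subjects. One is drop-out: "to account for that some subjects for some reason will terminate their participation". The other is division by MS level: "to get subjects with different levels of mutans streptococci to facilitate effects in strata of mutans streptococci levels".

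Three other places bear on the claim.

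- **Background:** in the investigators' own recent study, the strain "could colonize the oral cavity of 60-70% of subjects consuming them".
- **Study design and intervention:** there are two arms ("Subjects will be randomly selected to a test or a control group using SPSS"). No allocation ratio is given, and the trial is described as explorative.
- **Study group:** volunteers must be "healthy with no reported medical condition and no active caries lesions or periodontitis". No MS level is required at entry.

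The Aim section names metabolite profiles in plaque and the oral microbiota as the targets. The protocol gives no significance level for sizing, power, effect size, standard deviation, drop-out rate, target number of retainers, or number of MS strata.

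**The concern.** The sentence presents one number as sufficient for three separate demands: subjects who do not retain the bacteria, division by MS level, and drop-out. Yet 40 over two arms appears to do no more than match the group size of the precedent, so nothing is visibly set aside for any of the three. The one quantity the protocol does supply for such an allowance, the colonisation rate, takes the number of retainers in the test arm below 20.

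The precedent is also a weak guide. It concerns an effect on MS in subjects selected for high MS, whereas this trial takes mixed levels and studies microbiota and metabolite profiles.

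What is at stake is how results will be read. The section on the significance of the study presents the trial as able to decide whether probiotic exposure modifies the biofilm. If readers believe that 40 subjects guarantee enough retainers, and that strata and drop-out are provided for, a null result among retainers or within an MS stratum may be taken as evidence of no effect when it reflects small numbers.

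**Working it through.** **Inputs from the protocol.** Minimum total 40 (Study group; Statistical power). Benchmark: groups of 20 (Statistical power). Two arms (Study design and intervention). Colonisation 60-70% (Background).

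**Assumptions, because the protocol is silent.** 1:1 allocation; two-sided 5% t-test; 80% power; one unadjusted endpoint; drop-out of 15-20%; two equal MS strata.

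**Step 1: the plan's own figure.** The 40 cannot be reproduced as a power calculation because the inputs are not given. The only route to it from the protocol's figures is 2 arms × 20 = 40, with no allowance added. That route is an inference.

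**Step 2: expected retainers.** Test arm = 40 / 2 = 20.

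- Before drop-out: 20 × 0.60 = 12 to 20 × 0.70 = 14.
- 15% drop-out: 17 complete per arm; 17 × 0.60 = 10.2 to 17 × 0.70 = 11.9.
- 20% drop-out: 16 complete per arm; 16 × 0.60 = 9.6 to 16 × 0.70 = 11.2.
- Two equal strata, before drop-out: 12 / 2 = 6 to 14 / 2 = 7 per stratum, against 10 controls.

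For scale, 20 expected retainers would need 20 / 0.70 = 28.6, so 29, to 20 / 0.60 = 33.3, so 34, in the test arm before drop-out.

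**Step 3: detectable difference.** With n₁ and n₂ subjects, df = n₁ + n₂ − 2 and noncentrality = δ / √(1/n₁ + 1/n₂). Solve the noncentral t for the δ (in SD) that gives 80% power. Expected counts are used without rounding. The last column is the power at δ = 0.909, the effect that 20 v 20 detects with 80% power.

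| Comparison | n₁ v n₂ | Detectable δ (SD) | Power at 0.909 SD |
|---|---|---|---|
| All randomised | 20 v 20 | 0.909 | 80% |
| Retainers v controls, 70% | 14 v 20 | 1.007 | 72% |
| Retainers v controls, 60% | 12 v 20 | 1.057 | 67% |
| Same, with 15-20% drop-out | 11.9 v 17 to 9.6 v 16 | 1.10 to 1.19 | 64% to 57% |
| One of two strata, before drop-out | 7 v 10 to 6 v 10 | 1.48 to 1.56 | 41% to 37% |

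As a check, the normal approximation for 20 v 20 gives (1.960 + 0.842) × √(2/20) = 0.886, close to 0.909.

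These figures are favourable to the plan. The protocol intends false-discovery-rate adjustment for most analyses, which raises the difference needed for any one endpoint.

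**Step 4: the other reading of the benchmark.** If groups of 20 meant 20 in total, the benchmark is 10 per arm.

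- Retention: 12-14 against 10, so covered.
- Drop-out of 20%: 9.6-11.2 against 10, so nearly covered.
- Strata: 6-7 per stratum against 10, so not covered.

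**The case against.** The strongest reply is that the section contains no calculation, so there is none to fail. The protocol never says that 20 retainers is the sufficient number, and Study group ties 40 to earlier knowledge of acquisition, which suggests colonisation was considered. Forty is a minimum, and the trial is explorative. The strata wording is modest: it speaks of obtaining a spread of MS levels to help look for effects, and promises no powered test in each stratum. Taking mixed MS levels is a deliberate, stated choice.

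Much of this stands, and it rules out several stronger conclusions that a reader might draw.

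- **That 40 cannot serve the trial, or that there is certainly nothing in reserve.** This depends on reading the benchmark per arm. That is the more natural reading, but the cited studies are not at hand, and under the other reading retention is covered.
- **That underpowered stratum-by-stratum tests are planned.** None is specified.
- **That enrolment must rise.** An explorative trial may proceed at 40, and the 29-34 in Step 2 only shows the size of the gap.

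What does not stand is the defence of the sentence itself. The assurance is attached to the minimum of 40, not to some larger number that might be recruited. Being explorative excuses the absence of a formal calculation, but not a claim of sufficiency that the document's own colonisation rate does not bear out. Nor is this a matter left to an analysis plan, since the claim is made in the protocol.

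**Conclusion.** The concern holds as a defect of justification. On the per-arm reading and 1:1 allocation, 40 subjects only match the benchmark, and 12-14 retainers are expected in the test arm before drop-out. The detectable difference goes from about 0.91 SD for all randomised subjects to 1.01-1.06 SD for retainers v controls, and to about 1.10-1.19 SD with an assumed 15-20% drop-out. On the 20-in-total reading only the provision for strata clearly falls short. On either reading the benchmark comes from a different population and a different endpoint.

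The retainer count rests on the protocol's figures plus 1:1 allocation. The SD figures rest also on the assumed test, level and power. The stratum figures further assume two equal strata. No primary analysis is shown to be wrong and the remedy is wording, so this is a should-fix.

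**What to change.** Revise the Statistical power section, leaving enrolment as it is.

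1. Withdraw the assurance of enough retainers and the claim that 40 accounts for drop-out.
2. State that 40 gives about 20 per arm and, at 60-70% colonisation, 12-14 expected retainers in the test arm before drop-out. State the allocation ratio.
3. State the detectable difference for one unadjusted endpoint, with its assumptions (two-sided 5%, 80% power, t-test): about 0.91 SD for 20 v 20, 1.01-1.06 SD for retainers v controls, and about 1.10-1.19 SD for the latter if 15-20% drop out.
4. Say whether the precedent's groups of 20 are per arm or in total, and acknowledge that it concerns MS in high-MS subjects.
5. Label retainer and MS-stratum comparisons exploratory, and say that a null result there does not reject an effect.

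As an option outside the required change, effect modification by MS could be examined with one arm by continuous baseline MS interaction in all subjects. Its power at 40 has not been worked out here, so no gain is claimed.

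The cost is a change of protocol wording, and a stated sensitivity that looks less favourable than the present text.
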